4.9.1. First step: security analysis

In this stage of the study, 25 women will initially be included to determine the safety of the device during its use and up to 30 days after its removal. The main safety events to be considered in this analysis will be vaginal hemorrhage and uterine infection, both recorded according to the CTCAE version 4.0 criteria. Other adverse events that the researcher judges to be related to the use of the device will also be recorded (causal link at least possible).

The device will be considered unsafe and, consequently, the study will be interrupted if there is a single adverse event grade 3 or higher.

If no grade 3, 4 or 5 adverse events are recorded in this series of 25 cases, the study will proceed to the second stage after evaluation and recommendation by the Independent Data Monitoring Committee and also after analysis and approval of the partial (safety) report by the CEP/CONEP system.

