4.9.2. Second step: analysis of the effectiveness

The participants in the first stage will not be part of the second. Although the main objective of this step is to evaluate the effectiveness of the device in preventing post-conization cervical canal stenosis, safety and quality of life issues will also be analyzed. The observation period for the second stage will be two years.

In the second stage, 240 participants will be recruited randomly balanced 1: 1 in two groups: one who will receive the DUDA device after CAF and another who will not receive it. Randomization, active search and patient management will take place at the outpatient clinic after the signature of the TLCE by the nurse responsible for clinical research in the department and will be carried out in blocks of 4, through the REDCap program.

4.10. Study outcomes:

4.10.1. Device security:

The safety analysis will be performed up to 30 days after surgery. The definitions of CTCAE (Common Terminology Criteria for Adverse Events) version 4.0 will be adopted as a reference for the security assessment of the device. For that, two main safety events will be considered during its use: vaginal bleeding and uterine infection. Below are the gradations for the two main security events defined by CTCAE version 4.0.

a) Vaginal bleeding:

- Grade 1: mild bleeding, identified on clinical examination or imaging study. No intervention is indicated;
- Grade 2: moderate bleeding; Medical intervention is indicated;
- Grade3: bleeds, intense; need for a blood transfusion; radiological or endoscopic intervention is indicated;
- Grade 4: bleeding determines life-threatening; urgent surgical intervention is indicated;
- Grade 5: death from bleeding.

b) Uterine infection:

- Grade 1: (there is no category for this event);
- Grade 2: moderate symptoms; oral intervention is indicated (eg: antibiotics, antifungal, antiviral);
- Grade 3: intravenous intervention is indicated (eg: antibiotics, antifungal, antiviral); radiological intervention or surgical intervention are indicated;
- Grade 4: infection determines life-threatening; urgent surgical intervention is indicated;
- Grade 5: death from bleeding.

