Endocervical canal stenosis (early and late) will be assessed through clinical information and physical examination at each visit to the hospital after surgery. The participant will be asked about menstrual flow and dysmenorrhea during anamnesis, which would indirectly show whether the endocervical canal is patent or not. In the physical examination, after viewing the cervix through specular examination, the doctor will check the permeability of the canal by introducing the hysterometer through the cervical canal. The difficulty of introducing the 2.5mm hysterometer through the channel will be noted according to the following scale:

The possible passage of the hysterometer?

( ) No difficulty

( ) Little / Moderate difficulty, however possible passage of the hysterometer

( ) Could not pass

4.10.3. Quality of life:

Quality of life questionnaires are used in clinical trials and include important outcomes such as postoperative pain and related symptoms. For these assessments, in the present study, the following instruments will be used:

a) Functional Assessment of Cancer Therapy - Cervix Cancer (FACT-Cx), version 4.0, in Portuguese (Annex 1).

b) Universal Pain Assessment Tools: comprises the Visual Analog Pain Scale (VAS), the Numeric Visual Pain Scale (EVN) and the Faces Pain Scale (EF) (Annex 2).

4.11. Study interruption rules:

Below are the study interruption criteria:

a) Registration of a single grade 5 adverse event at any stage of the study;

b) Record of two grade 3 or 4 adverse events in the first stage of the study;

c) Record of two grade 3 or 4 adverse events in the second stage of the study;

d) the benefit of using the device under interim analysis;

e) Identification of considerable risk to participants not provided in this research protocol.

In any of the aforementioned situations, the researcher, before interrupting the study, will communicate the Research Ethics Committee (CEP) of the Barretos Cancer Hospital and await the substantiated opinion, unless the risk to the participants is imminent. In the latter situation, the researcher will interrupt the study to safeguard the research participants and will communicate the CEP as soon as possible.

4.12. Study visits and data collection:

TABLE 1 summarizes the activities carried out in the study according to the time of the visits.

4.12.1. Baseline visit:

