The researcher will record the surgical times for carrying out the CAF and for implanting the device. Such records will be performed separately following the datasheet at the time of surgery.

TABLE 1 - Summary of study activities according to the moment.

|  | ***Baseline*** | **Surgery** | **1- FUP** | **2-FUP** | **FUP-1** | **FUP-2** | **FUP-3** | **FUP-4** |
| --- | --- | --- | --- | --- | --- | --- | --- | --- |
| **Moment** | - | Day 0 | 15 days | 30 days | 3 months | 6 months | 12 months | 18 months |
| **Time of delay** | - | - | ± 3 days | ± 3 days | ± 10 days | ± 10 days | ± 10 days | ± 10 days |
| **Elegebility** | X |  |  |  |  |  |  |  |
| **Consent Information** | X |  |  |  |  |  |  |  |
| **Randomization** | X |  |  |  |  |  |  |  |
| **Surgery (LEEP)** |  | X |  |  |  |  |  |  |
| **Device** |  | X |  |  |  |  |  |  |
| **Medical History** |  |  | X | X | X | X | X | X |
| **Gynecologic exam** |  |  | X | X | X | X | X | X |
| **Time of remove device** |  |  |  | X |  |  |  |  |
| **Pap smear** |  |  |  |  | X | X | X | X |
| **Hysterometry** |  |  |  |  | X | X | X | X |
| **Colposcopy** |  |  |  |  | X | X | X | X |
| **QOL** | X | X | X | X | X | X | X | X |
| **Adverse events** |  |  | X | X | X | X | X | X |

FICT = Informed Consent Form, CAF = High frequency surgery, QOL = Quality of life, EA = Adverse event

NOTE: The safety analysis of the device will be performed until the 30th postoperative day.

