10. SCHEDULE

The study schedule after approval by the Research Ethics Committee is shown in Chart 3.

TABLE 3 - Study execution schedule.

| Study stage | Months elapsed after approval by the Research Ethics Committee | | | | | | | |
| --- | --- | --- | --- | --- | --- | --- | --- | --- |
|  | **1 – 3** | **4 – 6** | **7 – 9** | **10 – 12** | **13 – 15** | **16 – 18** | **19 – 21** | **22 - 24** |
| Inclusion (*1) | x | x |  |  |  |  |  |  |
| Follow up | x | x | x | x | x | x | x | x |
| Statistics Analysis (*2) | x | x |  |  |  |  | x | x |
| Preparation of the manuscript |  |  |  |  |  |  | x | x |
| Submission of the manuscript |  |  |  |  |  |  |  | x |

(* 1) The first stage of the study includes 25 participants for the safety analysis of the device (up to 30 days after surgery). The second stage will include 240 participants in each arm (randomized allocation: with and without the device). The recruitment estimate is 1 to 3 weeks in the first stage and 25 to 30 weeks in the second stage since the recruitment potential is 6 to 10 surgeries per week.

(* 2) An interim analysis is foreseen in the transition from the first to the second stage of the study and when the casuistry of the second stage reaches 25%, 50% and 75% of the recruitment estimate.

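### First-stage safety rule: section 4.9.1 stops the study at one grade 3 or higher event but section 4.11(b) at two, and the safety window has two different end dates

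*Protocol*

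**What the plan says.** **Threshold.** Section 4.9.1 considers the device unsafe at the first severe event: "the study will be interrupted if there is a single adverse event grade 3 or higher". Its condition for moving on is the mirror image: "If no grade 3, 4 or 5 adverse events are recorded in this series of 25 cases", the second stage follows, subject to the monitoring committee's recommendation and CEP/CONEP approval. Section 4.11 then lists the interruption criteria for the whole study. Two concern the first stage: "a) Registration of a single grade 5 adverse event at any stage of the study" and "b) Record of two grade 3 or 4 adverse events in the first stage of the study". Item (c) covers the second stage separately.

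**Window.** Section 4.9.1 assesses the safety of the device "during its use and up to 30 days after its removal". Three other places stop earlier:

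- Section 4.10.1: "The safety analysis will be performed up to 30 days after surgery".
- The note under Table 1 (study activities): "The safety analysis of the device will be performed until the 30th postoperative day".
- Footnote *1 to the schedule in section 10, which names the first stage and gives 30 days after surgery.

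Section 4.12.2 places removal at the 2-PO visit, day 30 with a tolerance of 3 days.

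**Grading scale.** Sections 4.9.1 and 4.10.1 grade events by CTCAE version 4.0. Section 4.12.2 has them recorded by version 3.0.

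**The concern.** A stopping rule should give one answer for every possible result, and it should be settled before the first event. Here a single grade 3 or 4 event makes the device unsafe under 4.9.1 but does not meet any numerical criterion in 4.11. The procedure in 4.11 for informing the ethics committee and awaiting its opinion is tied to the situations listed there. The event that 4.9.1 treats as decisive is therefore outside the protocol's own interruption procedure. If the choice of rule is left until such an event happens, it will be made with the result known.

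The window matters for a similar reason. A grade 3 bleed or infection in the month after removal counts under 4.9.1 and falls outside the analysis described in the other three places. The committee and CEP/CONEP could receive a safety report closed about 30 days too early by the standard of 4.9.1. This report feeds the decision to randomize 240 women, 120 of them to a new device. Section 7 itself describes the transition between stages as particularly critical.

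**Working it through.** The protocol derives no figure for the first-stage rule. Section 5.1 takes n = 25 from CONEP's advice, and no operating characteristics are given. There is therefore no stated number to reproduce, and the check compares the rules and sizes the disagreement.

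**1. The two thresholds side by side**

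| First-stage result | Section 4.9.1 | Section 4.11 (a) and (b) |
| --- | --- | --- |
| No grade 3–5 event | May proceed | Not met |
| Exactly one grade 3 or 4 event | Interrupt; may not proceed | Not met |
| Two or more grade 3 or 4 events | Interrupt | Interrupt |
| Any grade 5 event | Interrupt | Interrupt |

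Only the second row conflicts. Item (e) of 4.11 does not close the gap: it covers considerable risks that the protocol does not foresee, whereas bleeding and infection are foreseen in 4.9.1, 4.10.1 and 8.3.

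**2. How likely the conflicting result is**

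Inputs: n = 25 (sections 4.9.1 and 5.1). The true grade 3–4 rate p per woman is an assumption, taken as 1%, 2%, 5% and 10%. Each woman has at most one event, women are independent, and there is no grade 5 event.

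- One-event rule: P(≥1) = 1 − (1 − p)^25
- Conflict: P(exactly 1) = 25p(1 − p)^24
- Two-event rule: P(≥2) = P(≥1) − P(exactly 1)

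For p = 2%: P(≥1) = 1 − 0.98^25 = 0.397; P(exactly 1) = 25 × 0.02 × 0.98^24 = 0.308; P(≥2) = 0.089.

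| Assumed p | Interrupt, one-event rule | Interrupt, two-event rule | Exactly one event (rules conflict) |
| --- | --- | --- | --- |
| 1% | 22.2% | 2.6% | 19.6% |
| 2% | 39.7% | 8.9% | 30.8% |
| 5% | 72.3% | 35.8% | 36.5% |
| 10% | 92.8% | 72.9% | 19.9% |

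**3. The two windows**

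- Scheduled removal: day 30 ± 3, that is day 27 to 33.
- Window in 4.9.1: removal + 30 days = day 57 to 63.
- Window in 4.10.1, the Table 1 note and the schedule footnote: day 30.
- Difference: 57 − 30 = 27 to 63 − 30 = 33 days, or about 30 days. For scheduled removals this is essentially the whole post-removal period.

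After 2-PO, the next scheduled adverse-event record is at 3 months ± 10 days, so no planned contact falls at the end of the longer window. Section 4.10.1 does provide for collecting events that participants volunteer.

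**The case against.** The strongest reply is that 4.11 never gives permission to proceed. Only 4.9.1 says when the second stage may open, and with one grade 3 or 4 event that condition fails whatever 4.11(b) says. The committee and CEP/CONEP must agree in any case. This stands. The percentages above give the chance of reaching the conflict, not the chance of wrongly opening the second stage. What remains open is whether the study is interrupted after one event, including whether further first-stage women receive the device, and by what procedure. A patient-safety stopping rule should not leave that open.

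A second reply is that 4.9.1 is the more specific text and so prevails. The protocol does not say so, and 4.11(b) is equally specific, since it names the first stage. If 4.9.1 prevailed, 4.11(b) would have no effect of its own.

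A third is that 4.9.1 might mean device-related events and 4.11(b) events of any cause. The stop sentence in 4.9.1 refers to adverse events without that restriction, so the text does not support this reading.

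On the window, the stop and proceed clauses carry no day limit, and later events are still recorded at 3 months and beyond. Section 4.8 also allows early removal, in which case the longer window ends sooner and the shorter one includes some time after removal. These points reduce the gap for some women and show that the conflict lies in the analysis cut-off, not in whether later events are recorded. They do not reconcile the two cut-offs. Because the schedule footnote names the first stage, the shorter window cannot be set aside as second-stage text. It is also true that three of the four places agree on the shorter window, so changing 4.9.1 alone would be the smallest edit. It would, however, leave essentially no observation after a scheduled removal.

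**Conclusion.** The concern holds and must be fixed. The first-stage interruption rule gives opposite answers for exactly one grade 3 or 4 event, and no text settles which applies. At assumed true rates of 1% to 10% per woman, that result has a probability of about 20% to 37%, so it is a realistic outcome. These figures rest on the assumed rates, independence between women and at most one event per woman. The contradiction itself rests on the text alone. The safety window differs by about 30 days for women whose device is removed on schedule, and by less after early removal. The threshold is the more serious of the two. The CTCAE version mismatch is minor.

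**What to change.** - **Threshold:** change 4.11(b) to one grade 3 or higher event in the first stage, in line with the stricter stop and proceed clauses of 4.9.1. If the committee and CEP/CONEP prefer two events, change both clauses of 4.9.1 instead.
- **Window:** for the first-stage decision, use 30 days after removal in 4.10.1, the Table 1 note and schedule footnote *1. Do not close the safety report until every woman's window has ended. Confirm each woman's adverse-event status at that point, for example by a brief telephone call.
- **Grading:** replace CTCAE version 3.0 with 4.0 in 4.12.2.

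The cost is a short amendment, about 25 brief contacts and about 30 more days before the first-stage decision. The one-event rule is also strict: at an assumed true rate of only 1% it interrupts the study 22% of the time, against 2.6% for the two-event rule. The committee should accept that knowingly when it confirms the threshold.

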4.9.2. Second step: analysis of the effectiveness

The participants in the first stage will not be part of the second. Although the main objective of this step is to evaluate the effectiveness of the device in preventing post-conization cervical canal stenosis, safety and quality of life issues will also be analyzed. The observation period for the second stage will be two years.

In the second stage, 240 participants will be recruited randomly balanced 1: 1 in two groups: one who will receive the DUDA device after CAF and another who will not receive it. Randomization, active search and patient management will take place at the outpatient clinic after the signature of the TLCE by the nurse responsible for clinical research in the department and will be carried out in blocks of 4, through the REDCap program.

4.10. Study outcomes:

4.10.1. Device security:

The safety analysis will be performed up to 30 days after surgery. The definitions of CTCAE (Common Terminology Criteria for Adverse Events) version 4.0 will be adopted as a reference for the security assessment of the device. For that, two main safety events will be considered during its use: vaginal bleeding and uterine infection. Below are the gradations for the two main security events defined by CTCAE version 4.0.

a) Vaginal bleeding:

- Grade 1: mild bleeding, identified on clinical examination or imaging study. No intervention is indicated;
- Grade 2: moderate bleeding; Medical intervention is indicated;
- Grade3: bleeds, intense; need for a blood transfusion; radiological or endoscopic intervention is indicated;
- Grade 4: bleeding determines life-threatening; urgent surgical intervention is indicated;
- Grade 5: death from bleeding.

b) Uterine infection:

- Grade 1: (there is no category for this event);
- Grade 2: moderate symptoms; oral intervention is indicated (eg: antibiotics, antifungal, antiviral);
- Grade 3: intravenous intervention is indicated (eg: antibiotics, antifungal, antiviral); radiological intervention or surgical intervention are indicated;
- Grade 4: infection determines life-threatening; urgent surgical intervention is indicated;
- Grade 5: death from bleeding.

Other events in which the researcher believes that there is a possible, probable or definitive relationship with the device (during or after its use) other than the two mentioned above will also be classified according to CTCAE version 4.0. Information about all adverse events provided voluntarily by the research participant, discovered by the researcher's questions or detected by physical examination, laboratory tests or other means, will be collected, recorded in the medical record and monitored as appropriate.

Clinical conditions/illnesses present before starting study treatment are considered adverse events when they worsen after the start of study treatment (any procedure specified in the protocol). Adverse events that occur before the study treatment begins, but after signing the informed consent form will be recorded in the medical record. Laboratory values ​​or abnormal test results are only adverse events if they induce clinical signs or symptoms or require therapy, and will also be recorded. The data of adverse events will be extracted from the original documents, reviewed by the responsible researcher and inserted in the study database. For the purposes of this study, the following definitions will be considered:

• Adverse event: any undesirable sign, symptom or clinical condition that occurs after the start of study therapy, even if it is not considered to be related to study therapy.

• Serious adverse event: any medical event that results in: death, adverse life-threatening surgical experience, hospitalization or prolonged hospitalization, persistent or significant disability/disability, or congenital anomaly. Important medical events that do not result in death, are life-threatening or require hospitalization can be considered as serious when, based on the appropriate clinical opinion, put the patient at risk or require medical or surgical interventions to avoid one of the results indicated in this definition.

4.10.2. Efficiency:

Endocervical canal stenosis (early and late) will be assessed through clinical information and physical examination at each visit to the hospital after surgery. The participant will be asked about menstrual flow and dysmenorrhea during anamnesis, which would indirectly show whether the endocervical canal is patent or not. In the physical examination, after viewing the cervix through specular examination, the doctor will check the permeability of the canal by introducing the hysterometer through the cervical canal. The difficulty of introducing the 2.5mm hysterometer through the channel will be noted according to the following scale:

The possible passage of the hysterometer?

( ) No difficulty

( ) Little / Moderate difficulty, however possible passage of the hysterometer

( ) Could not pass

4.10.3. Quality of life:

Quality of life questionnaires are used in clinical trials and include important outcomes such as postoperative pain and related symptoms. For these assessments, in the present study, the following instruments will be used:

a) Functional Assessment of Cancer Therapy - Cervix Cancer (FACT-Cx), version 4.0, in Portuguese (Annex 1).

b) Universal Pain Assessment Tools: comprises the Visual Analog Pain Scale (VAS), the Numeric Visual Pain Scale (EVN) and the Faces Pain Scale (EF) (Annex 2).

4.11. Study interruption rules:

Below are the study interruption criteria:

a) Registration of a single grade 5 adverse event at any stage of the study;

b) Record of two grade 3 or 4 adverse events in the first stage of the study;

c) Record of two grade 3 or 4 adverse events in the second stage of the study;

d) the benefit of using the device under interim analysis;

e) Identification of considerable risk to participants not provided in this research protocol.

In any of the aforementioned situations, the researcher, before interrupting the study, will communicate the Research Ethics Committee (CEP) of the Barretos Cancer Hospital and await the substantiated opinion, unless the risk to the participants is imminent. In the latter situation, the researcher will interrupt the study to safeguard the research participants and will communicate the CEP as soon as possible.

4.12. Study visits and data collection:

TABLE 1 summarizes the activities carried out in the study according to the time of the visits.

4.12.1. Baseline visit:

At the time of the initial visit, preoperative tests (blood count, serum biochemistry, coagulogram, chest X-ray, electrocardiogram and pregnancy test) and pre-anesthetic evaluation of women in whom CAF is indicated will be checked. This preoperative assessment is done on a routine basis and does not include specific aspects of the study. Women who are eligible for CAF and meet the study's eligibility criteria will be invited to participate in the survey. Those who agree will sign the Informed Consent Form at the initial visit.

During this visit, demographic and clinical information will be collected through interviews and consultation of medical records (Annexes 3). At this time, the quality of life questionnaires will also be applied.

4.12.2. Operative and postoperative visits:

On the day of surgery, a form will be filled out with the data pertinent to the surgical procedure. (Annex 4).

Postoperative visits will take place 15 days (1-PO) and 30 days (2-PO) after surgery. (Annexes 5 and 6). The acceptable windows of opportunity for visits will be ± 3 days. During these visits, the participants will undergo a medical consultation, when anamnesis and gynecological physical examination will be carried out. They will also answer the quality of life questionnaires. Any adverse event will be recorded on a specific form each post-operative visit in accordance with the Common Terminology Criteria for Adverse Events v3.0 (CTCAE V3). (Annex 7).

Participants who have the DUDA device will have it removed during the 2-PO visit during the gynecological examination.

4.12.3. Follow-up visits:

Follow-up visits will take place 3, 6, 12 and 18 months after surgery (respectively FUP-1, FUP-2, FUP-3 and FUP-4) according to our flow chart described below. The acceptable windows of opportunity for visits will be ± 10 days. During these visits, participants will undergo a medical consultation, when anamnesis and gynecological physical examination will be performed, which will include the collection of material for cervical cytology, hysterometry to assess the permeability of the endocervical canal and colposcopy to visualize the squamocolumnar junction. The degree of permeability of the channel will be recorded in a specific form. During follow-up visits, quality of life questionnaires will also be applied and adverse events will be recorded and follow-up information will be collected (Annex 8-11).

4.12.4. Surgery information:

The researcher will record the surgical times for carrying out the CAF and for implanting the device. Such records will be performed separately following the datasheet at the time of surgery.

TABLE 1 - Summary of study activities according to the moment.

|  | ***Baseline*** | **Surgery** | **1- FUP** | **2-FUP** | **FUP-1** | **FUP-2** | **FUP-3** | **FUP-4** |
| --- | --- | --- | --- | --- | --- | --- | --- | --- |
| **Moment** | - | Day 0 | 15 days | 30 days | 3 months | 6 months | 12 months | 18 months |
| **Time of delay** | - | - | ± 3 days | ± 3 days | ± 10 days | ± 10 days | ± 10 days | ± 10 days |
| **Elegebility** | X |  |  |  |  |  |  |  |
| **Consent Information** | X |  |  |  |  |  |  |  |
| **Randomization** | X |  |  |  |  |  |  |  |
| **Surgery (LEEP)** |  | X |  |  |  |  |  |  |
| **Device** |  | X |  |  |  |  |  |  |
| **Medical History** |  |  | X | X | X | X | X | X |
| **Gynecologic exam** |  |  | X | X | X | X | X | X |
| **Time of remove device** |  |  |  | X |  |  |  |  |
| **Pap smear** |  |  |  |  | X | X | X | X |
| **Hysterometry** |  |  |  |  | X | X | X | X |
| **Colposcopy** |  |  |  |  | X | X | X | X |
| **QOL** | X | X | X | X | X | X | X | X |
| **Adverse events** |  |  | X | X | X | X | X | X |

FICT = Informed Consent Form, CAF = High frequency surgery, QOL = Quality of life, EA = Adverse event

NOTE: The safety analysis of the device will be performed until the 30th postoperative day.

